Answer all questions accurately and completely in order to provide the PHRC with the relevant information to assess the risk-benefit ratio for the study. Do not leave sections blank.

### SPECIFIC AIMS

Concisely state the objectives of the study and the hypothesis being tested.

The main objective of this study is to test an intervention to increase the physical activity of medical residents, an employee population with little time for exercise. Specifically, the aims of this study are:

1. To determine if providing medical residents with an activity device that measures steps, distance, and calories burned and tracks this information over time on a website increases residents’ physical activity levels as measured by number of steps per day compared to a control group using a blinded activity device (no feedback).
2. To determine if an unblinded team competition using the activity device directly following the randomized phase increases residents’ activity level compared to baseline.
3. To determine if activity level is associated with change in weight during the residency year.
4. To determine if the average hours of sleep per week is associated with changes in weight and with activity level.

# BACKGROUND AND SIGNIFICANCE

Provide a brief paragraph summarizing prior experience important for understanding the proposed study and procedures.

Poor diet and physical inactivity accounted for 400,000 deaths in 2000 and will soon overtake tobacco as the leading cause of mortality in the United States. Poor diet and physical inactivity are associated with many chronic diseases, including cardiovascular diseases, diabetes, and cancer, and are associated with high health care costs. The worksite is an ideal setting for promoting physical activity and nutrition because it has already established channels of communication, support networks, and opportunities for developing corporate norms. Health promotion programs in the workplace have been shown to improve cardiovascular risk factors and reduce health care costs.

Massachusetts General Hospital has sponsored an employee physical activity and nutrition program since June 2005. Over 3000 employees have participated in this program since it was first started. However, none of the participants have been medical residents. The residents have been unable to participate in the 12-week program because of their busy clinical schedules. Medical residents have little time for self-care, including nutrition and physical activity. Poor health habits established during residency may contribute to weight gain and sedentary lifestyle long after the residency has been completed. Although there are many studies of resident burnout, there is a lack of studies addressing health promotion among residents.

Pedometers are relatively inexpensive devices usually worn on the hip that measure number of steps walked per day. A systematic review of 26 studies of pedometers concluded that pedometer use is associated with significant increases in physical activity and significant decreases in body mass index and blood pressure. A pedometer can easily be worn in a work environment and could potentially serve as a motivation to be more active while at work.

An activity monitor is similar to a pedometer, but it provides information about not only steps but also about speed and intensity of activities. The objective of the proposed research is to test an activity monitor as a tool to increase medical residents’ physical activity by increasing steps taken both at work and at home.

###### RESEARCH DESIGN AND METHODS

Briefly describe study design and anticipated enrollment, i.e., number of subjects to be enrolled by researchers study-wide and by Partners researchers. Provide a brief summary of the eligibility criteria (for example, age range, gender, medical condition). Include any local site restrictions, for example, “Enrollment at Partners will be limited to adults although the sponsor’s protocol is open to both children and adults.”

All 170 residents in Medicine at Massachusetts General Hospital will be invited to join the Be Fit program during the time period July-November 2010. Be Fit will be a program for the residents that provides nutrition information and counseling, free access to the on-site gym at MGH, and the opportunity to work with a personal trainer. If a resident signs up for Be Fit and completes the baseline physical assessment, he or she will be eligible for participating in the research study of the activity monitor. If a resident does not enroll in Be Fit, he or she is not eligible to participate in the research study. It is anticipated that approximately 100 residents will enroll in the research study.

Briefly describe study procedures. Include any local site restrictions, for example, “Subjects enrolled at Partners will not participate in the pharmacokinetic portion of the study.” Describe study endpoints.

All medicine residents rotate through a 4 week ambulatory block between July and November 2010. During this ambulatory block, each group of approximately 34 residents will be introduced to the Be Fit program and to the research study during a 1 hour session as part of their ambulatory block lecture series. The PI or one of the research staff members will review the consent form during this time with all the residents. Residents will be given the consent form to take home with them if they would like more time to read it over and will be given the opportunity to ask questions about the study. In order to participate in the research study, a resident must sign the consent form prior to the end of November.

Be Fit program:

All medicine residents will be given the opportunity to enroll in the Be Fit program during their ambulatory block rotation between July and November 2010. If a resident signs up for Be Fit, he or she will participate in a baseline assessment. During this assessment, the resident’s height, weight, waist circumference, body fat, blood pressure, and pulse will be measured. The resident will also have fasting blood test for a lipid profile. This same assessment will be repeated in May 2011. All measurements will be summarized in a letter that is emailed to the resident. The letter sent in May will compare the baseline measurements to the end of program measurements.

All residents who enroll in the Be Fit program (but not necessarily the research study) will be given a card for 36 free visits at on-site gym at MGH (Clubs at Charles River Park) between January and June 2011. In addition, the residents will be able to schedule up to 12 hours of personal training at the gym.

The nutrition education will take place during noon conference lunches, which are provided for all MGH medicine residents daily on Monday-Friday. These lunches are ordered by the Department of Medicine from local restaurants. Starting in January 2011, one of the noon lunches each week will be a “Be Fit” lunch that is lower in fat and calories than one of the typical noon lunches (i.e. Indian food, pizza, Thai food). In addition, the Be Fit nutritionists will provide nutrition information for all lunches during the week. For example, the number of calories and fat in one slice of pepperoni pizza or in one serving of pad thai will be posted at the table where the residents get their food. As part of the Be Fit program, residents will be given the opportunity to meet individually with a nutritionist twice during the period between January and June 2011.

Research study:

Residents who sign the informed consent will participate in the research study starting in January 2011. The research study will consist of 2 phases. In the first phase, half of the study subjects will be randomized to wearing an activity monitor with feedback, and half will be randomized to wearing an activity monitor with no feedback (blinded/control group). This phase will last for 6 weeks. Immediately following the randomized phase, all subjects will be unblinded and wear the activity monitor with feedback. The second phase will be a team competition between the 3 classes of residents (interns, juniors, and seniors). The teams will compete on average number of steps per week for each team. The team competition will last for 6 weeks.

Randomization: Study participants will be randomized in late December to either the intervention arm (activity monitor with feedback) or the control arm (activity monitor with no feedback). The randomization will be stratified by class year (intern, junior, senior).

Parameters to be measured:

The parameters that will be measured for all Be Fit program participants at baseline and at the end of the program are listed in the table below. The survey will collect data on health habits, including smoking, nutrition, physical activity, and sleep.

|  | Baseline  (July-November 2010) | End of program  (May 2011) |
| --- | --- | --- |
| **Physical assessment:** Blood pressure and heart rate, weight, BMI, body fat, waist circumference | X | X |
| **Blood draw:** Fasting lipids | X | X |
| Survey (completed by participant) | X | X |

For those Be Fit participants who enroll in the research study, we will collect data measured by the activity device worn from January through May 2011. The activity device records data on number of steps per day, number of calories burned per day, number of hours slept per night, and number of times awakened per night.

Device to be used: The “Fitbit”: Each study subject will be given a Fitbit, an activity monitor that wirelessly uploads data through a receiving device connected to the subject’s home computer. The activity monitor will be purchased from Fitbit, Inc, and ambulatory monitoring technology company. The Fitbit Tracker contains a motion sensor like the ones found in the Nintendo Wii, and it senses motion in three dimensions. The Tracker measures the intensity and duration of physical activities, calories burned, steps taken, distance traveled, how long it takes to fall asleep, and the amount of time asleep. The Fitbit is worn on the torso, including the waist or chest. It can also be clipped to an undergarment or carried in a pocket. The Fitbit needs to be charged every 5-10 days on a base station that plugs into a computer. It typically takes 60-90 minutes to fully charge. Each study subject will be assigned an anonymous gmail account and a study identification number that will be used to set up the personal Fitbit account. The key linking the subject’s name to the gmail account and the study ID will be stored in a file on the principal investigator’s Partners-protected computer. Study subjects will be able to access their personal Fitbit website by entering the gmail address and the study ID.

Randomized phase: Half of the subjects will be randomized to wearing the Fitbit with feedback. These subjects will be able to see the number of steps walked, calories burned, and distance traveled for each day. On the Fitbit website, the subject will have access to a personalized Fitbit website to view his or her daily and weekly totals of all measurements. Subjects randomized to the control group will wear the activity device but will not be able to see any of the measurements on the device or on the website. Subjects in the control group will receive email reminders to charge their Fitbit since they will not be able to view the battery icon on the device while it is blinded. The randomized phase will last for 6 weeks.

Team competition phase: Immediately following the randomization phase, all study participants will be unblinded and able to view the Fitbit feedback both on the device and on the website. The control group will be given a password to be able to log on to their personalized Fitbit website. The residents will be divided into 3 teams based on their class: interns, juniors, or seniors. The teams will compete on the average number of steps per week. The team standings will be displayed on the Fitbit website that will be viewed by each study subject. Teams will compete for 6 weeks.

Data to be collected:

Physical assessment*:* All residents who enroll in the Be Fit program will be asked to attend a physical assessment at baseline (between July and November 2010) and at the end (May 2011). All physical assessments will be conducted prior to 10 o’clock in the morning. During these visits, study staff collect weight, height, waist measurements, body fat, blood pressure, and heart rate.

Fasting blood test*:* During each physical assessment, residents enrolled in Be Fit undergo a fasting blood test for lipids. Residents are asked not to have anything to eat or drink after midnight the day before the test.

Survey: All residents enrolled in Be Fit will complete a survey at baseline and at the end of the program. The survey collects information on smoking history, physical activity, and nutritional habits. Age, sex, race/ethnicity, marital status, education level, and care for dependents at home (children, disabled/ill spouse, parent, or child) will be recorded on the survey. The survey also includes a scale that measures psychological stress, called the Schwartz Outcome Scale-10 © (SOS-10 TM). The SOS-10 is a 10 item survey tool to determine a person’s distress level. It is not a diagnostic instrument and cannot be used for making psychiatric diagnoses. The scores range from 0 to 60. Higher scores reflect better psychological health and lower scores indicate emotional distress and lower levels of psychological health. There is a cut off score of 43, and a change of 8 points or greater are a reliable indicator that a person’s psychological status has either improved or deteriorated.

Data from Fitbit website: Only residents who enroll in the research study will be given a Fitbit activity device. All activity data and sleep data recorded during the study period will be collected. The Fitbit website provides individual data on the number of steps per day, the number of calories burned per day, and the number of hours slept per 24 hour period. This data will be collected from all study subjects during both the randomized phase and the team competition phase of the study.

Study endpoints:

Primary endpoint: The primary endpoint of the study will be average activity level per resident as measured by number of steps per day. In the randomized phase, the average number of steps per day in the intervention group (Fitbit + feedback) will be compared to the average number of steps per day in the control group (Fitbit without feedback). In the second phase, we will compare the change in the average number of steps for each participant compared to their own baseline number of steps from the first phase.

Secondary endpoints: Secondary endpoints will be change in weight during the study period and number of hours of sleep per 24 hour period for each resident. Survey data will be used to examine reported changes in physical activity levels, nutritional habits, and sleep habits. The survey data will also provide data from the SOS-10 scale on change in psychological stress.

Statistical methods:

In the randomized phase, the average number of steps per day in the intervention group (Fitbit + feedback) will be compared to the average number of steps per day in the control group (Fitbit without feedback) using a two-sample t test or a Wilcoxon rank sum test whichever is more appropriate. To determine whether team competition increases activity level, the primary and secondary endpoints from the second phase will be compared to results from the first phase using paired t-tests. The changes in primary and secondary endpoints during study periods will be compared between the two randomization groups using a two-sample t test, and compared among the residency year groups using an analysis of variance approach. To determine if the average hours of sleep per week is associated with changes during study period, Pearson or Spearman correlation coefficients will be used to summarize the correlation between sleep time and change in weight/number of steps.

Power analysis: For the randomization phase, a sample size of 50 in each group will have 84% power to detect a difference in means of 1200 steps assuming that the common standard deviation is 2000 steps using a two group t-test with a 0.05 two-sided significance level.

For studies involving treatment or diagnosis, provide information about standard of care at Partners (e.g., BWH, MGH) and indicate how the study procedures differ from standard care. Provide information on available alternative treatments, procedures, or methods of diagnosis.

This study does not involve treatment or diagnosis of a medical condition or illness.

Describe how risks to subjects are minimized, for example, by using procedures which are consistent with sound research design and which do not unnecessarily expose subjects to risk or by using procedures already being performed on the subject for diagnostic or treatment purposes.

The risk associated with this research is minimal. The principle investigator oversees all study staff to ensure that procedures are followed which are consistent with sound research design and do not expose subjects to unnecessary risk. The study does not offer a diagnosis or treatment to subjects. The procedures in study were developed using standard nutrition and fitness guidelines and recommendations.

Describe explicitly the methods for ensuring the safety of subjects. Provide objective criteria for removing a subject from the study, for example, objective criteria for worsening disease/lack of improvement and/or unacceptable adverse events. The inclusion of objective drop criteria is especially important in studies designed with placebo control groups.

Subjects will be withdrawn from the study if they leave their employment at MGH or if they request to be removed from the study.

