**RECRUITMENT PROCEDURES**

Explain in detail the specific methodology that will be used to recruit subjects. Specifically address how, when, where and by whom subjects will be identified and approached about participation. Include any specific recruitment methods used to enhance recruitment of women and minorities.

Every Medicine resident rotates through a 4 week ambulatory block between July and November 2010. During this ambulatory block, each group of approximately 34 residents will be introduced to the Be Fit program and to the research study during a 1 hour session as part of their ambulatory block lecture series. If a resident chooses to participate in the Be Fit program, he or she will be asked to participate in the research study.

Provide details of remuneration, when applicable. Even when subjects may derive medical benefit from participation, it is often the case that extra hospital visits, meals at the hospital, parking fees or other inconveniences will result in additional out-of-pocket expenses related to study participation. Investigators may wish to consider providing reimbursement for such expenses when funding is available

To increase compliance with wearing the device on a regular basis, we will offer a small gift certificate at the hospital coffee shop as an incentive. All residents who wear the device regularly will be eligible each week to be entered into a raffle for the gift certificate. At the end of each week, we will calculate the number of days each resident has worn their Fitbit. All residents who have worn their Fitbit for 5 of the previous 7 days will be put into a raffle to win a $10 gift certificate for Coffee Central at MGH. The winner each week will be announced in the weekly email to all the study participants. We will conduct this raffle once a week for the entire 12 week study period.

At the end of the study, If the participant wears the Fitbit activity device for 75% of the intervention period (12 weeks), the study participant will be allowed to keep the device (retail value of $99.00) for their own personal use.

For guidance, refer to the following Partners policies:

Recruitment of Research Subjects

[**http://healthcare.partners.org/phsirb/recruit.htm**](http://healthcare.partners.org/phsirb/recruit.htm)

Guidelines for Advertisements for Recruiting Subjects

[**http://healthcare.partners.org/phsirb/advert.htm**](http://healthcare.partners.org/phsirb/advert.htm)

Remuneration for Research Subjects

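### The weight-change endpoint does not match the two weights taken: they are about 5 to 11 months apart, and the stated tests on raw change ignore the difference in elapsed time

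*Protocol*

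**What the plan says.** Four parts of the protocol bear on the weight endpoint.

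- **Endpoint.** Under Study endpoints: "Secondary endpoints will be change in weight during the study period". Specific Aims, Aim 3, instead speaks of weight change over the residency year.
- **Study period.** Under Research study: "Residents who sign the informed consent will participate in the research study starting in January 2011". Randomization comes shortly before: "Study participants will be randomized in late December to either the intervention arm". Recruitment Procedures gives the length: "We will conduct this raffle once a week for the entire 12 week study period". Those weeks are six of randomized feedback versus no feedback, then six of team competition with everyone unblinded.
- **Weight measurements.** Under Data to be collected, Be Fit enrollees "will be asked to attend a physical assessment at baseline (between July and November 2010) and at the end (May 2011"). Enrolment is staggered: "All medicine residents will be given the opportunity to enroll in the Be Fit program during their ambulatory block rotation between July and November 2010". There is one repeat: "This same assessment will be repeated in May 2011". No weight is scheduled at randomization, at week 6 or at week 12.
- **Tests.** Statistical methods names a two-sample t test for changes between arms, analysis of variance across residency years, Pearson or Spearman correlation of sleep with weight change, and paired t-tests of phase 2 against phase 1 for both primary and secondary endpoints. None is said to allow for time between measurements.

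**The concern.** The endpoint as worded covers 12 weeks from January 2011, and the scheduled weights cannot supply it. What they supply is a change that starts before randomization, by an amount that depends on when the resident's ambulatory block fell, and that ends in May.

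This has three consequences:

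1. Raw changes over unequal intervals are analysed as if they were alike. Part of the variation between residents is then elapsed time, not response.
2. Device data begin only in January. For a resident weighed in July, the activity and sleep data that are meant to explain the weight change are missing for a large part of the interval. If block timing is related to class year, activity or sleep, elapsed time becomes a confounder of the non-randomized analyses behind Aims 3 and 4 and of the class-year comparison.
3. By May both arms have had feedback since the end of week 6. The arm contrast on weight is therefore immediate versus six-week-delayed feedback.

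Separately, two weights give one change per resident, so a phase 2 versus phase 1 comparison of weight does not exist.

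**Working it through.** **The plan's own figure.** The protocol gives no figure for the weight interval. Its one computed figure is power for steps. With 50 per arm, a difference of 1200 and an SD of 2000, the noncentrality is 1200 / (2000 × √(2/50)) = 1200/400 = 3.0. The noncentral t with 98 degrees of freedom gives 84.4%, against the stated 84%. It reproduces, and nothing below touches it.

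**Inputs.** From the protocol: baseline weight 1 July to 30 November 2010; end weight May 2011; randomization in late December; study start in January 2011; 12 weeks (84 days), with the arms differing for 6 weeks (42 days). Assumptions: randomization on 20 to 31 December, May visit on 1 to 31 May.

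**Interval and share before randomization.** Interval = May date − baseline date. Share = (randomization date − baseline date) / interval.

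| Baseline | Interval, days (1 May to 31 May) | Days before randomization | Share before randomization |
|---|---|---|---|
| 1 July | 304 to 334 | 172 to 183 | 172/334 = 52% to 183/304 = 60% |
| 15 September | 228 to 258 | 96 to 107 | 96/258 = 37% to 107/228 = 47% |
| 30 November | 152 to 182 | 20 to 31 | 20/182 = 11% to 31/152 = 20% |

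**Ratio of longest to shortest interval.** With the same May date it is 304/152 = 2.0 (1 May) down to 334/182 = 1.8 (31 May). Pairing opposite ends of May gives 334/152 = 2.2. Mid-July and mid-November baselines with a mid-May visit give 305/182 = 1.7.

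**Typical spread.** If baselines fall evenly over the 152-day window and visits evenly over May (assumption), the mean interval is 319 − 76 = 243 days. The SD is √(152²/12 + 30²/12) = 45 days, a coefficient of variation of 18%. The mean share before randomization is about 40%.

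**Fit to the 12 weeks.** 84/334 = 25% to 84/152 = 55% of the measured interval. Twelve weeks from 1 January end on 26 March and from 31 January on 25 April, so the May weight also falls after the period. The arms differ for 42/334 = 13% to 42/152 = 28% of the interval.

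**Noise in the arm comparison.** With even spread, baseline timing has an SD of 5/√12 = 1.44 months. For an assumed gain of 0.2 to 0.5 kg per month this contributes an SD of 0.29 to 0.72 kg. Against an assumed SD of weight change of 2 to 3 kg, the total becomes √(3² + 0.29²) = 3.01 at one end and √(2² + 0.72²) = 2.13 at the other, an increase of about 0.5% to 6%.

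**The case against.** The strongest defence is that the July–November to May schedule roughly suits Aim 3, which is about the residency year, and that the study period may be a loose phrase. The protocol also speaks of wearing the device from January through May. That stands in part: the schedule is not mistimed for Aim 3. But the endpoint and the aim then name different spans, and no weight is taken in January under either reading of the study period.

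The six-week delay is openly described, and no aim claims a feedback effect on weight. True, but Statistical methods does compare changes in secondary endpoints between arms, so that contrast should be described for what it is.

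Nor can the matter be left to an unseen statistical analysis plan. The protocol itself names the tests, and they do not fit its own schedule.

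Three stronger readings are tempting and are not supported:

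- *Much of the weight change precedes randomization.* The dates show only how much of the time does. When weight is gained or lost cannot be known from the protocol, and for the latest baselines even the time share is only 11% to 20%.
- *The arm comparison is biased.* Randomization follows the baseline weight, so unequal intervals are balanced between arms in expectation. They cost precision only.
- *The distortion amounts to 1.0 to 2.5 kg.* That is the five-month window times the assumed 0.2 to 0.5 kg per month. It compares the earliest with the latest resident. The tests respond to the SD, which is much smaller.

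Confounding of the class-year, activity and sleep analyses is likewise a possibility. The protocol does not say how residents are allocated to blocks, so a link between block timing and those factors is neither shown nor excluded.

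**Conclusion.** The point holds as a mismatch between a secondary endpoint, its schedule and its tests. The interval between weights is about 5 to 11 months at the extremes, with a ratio of 1.8 to 2.0 for a common May date. About 11% to 60% of the elapsed time precedes randomization, depending on the baseline date and on the assumed late-December and May dates.

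For the arm comparison the effect is modest noise without expected bias, an SD larger by about 0.5% to 6% under the assumptions shown. For the non-randomized analyses it is a possible confounder, conditional on how blocks were assigned. For the paired phase comparison the defect is definite, because weight cannot be analysed that way with two measurements. The primary endpoint and its power are unaffected.

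**What to change.** - Redefine the endpoint as change in weight from Be Fit baseline (July–November 2010) to May 2011, and reconcile the wording of Aim 3 and Study endpoints with it.
- In place of the t test, analysis of variance and correlations on raw weight change, fit a linear model of May weight with baseline weight, weeks between the two assessments and class year. Add arm for the randomized contrast, steps for Aim 3, or sleep for Aim 4. Class year is already the stratification factor; its coefficients serve the comparison among residency years.
- Describe the arm contrast on weight as immediate versus six-week-delayed feedback.
- Exclude weight from the paired phase 2 versus phase 1 comparison.

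The model allows for unequal intervals but does not turn the baseline into a weight at randomization. That is why the endpoint must also be renamed. The cost is a change of wording and a standard regression, with no new measurement. It needs the date of each assessment, which one would expect to be on file, although the protocol does not say so.

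### The primary step comparison leaves recorded baseline covariates unused, and a pooled phase 2 versus phase 1 test would credit half the feedback effect to the team competition

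*Protocol*

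**What the plan says.** All references are to the Protocol, Research Design and Methods.

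- **Timing.** Randomization is in late December, stratified by class year, and the device is worn from January. Steps are collected only in the randomized phase and the team competition phase. No device run-in is described.
- **Phase 1.** "half of the study subjects will be randomized to wearing an activity monitor with feedback"; the other half wear a blinded device. The analysis is a two-sample t test or a Wilcoxon rank sum test, with no covariate.
- **Phase 2.** Everyone receives feedback and the competition begins. The endpoint is each participant's change "compared to their own baseline number of steps from the first phase". Statistical methods assigns paired t-tests to this and does not say whether they are run by arm. Changes are also to be compared between the randomized groups with a two-sample t test.
- **Recorded before randomization.** "The survey collects information on smoking history, physical activity, and nutritional habits", and it also records sex. It is completed between July and November. Class year is known as the stratification factor.
- **Power.** "50 in each group will have 84% power to detect a difference in means of 1200 steps", assuming "the common standard deviation is 2000 steps".

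**The concern.** Two separate matters follow from having no step count before randomization.

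First, the primary test compares follow-up means only. Stable differences between residents in habitual activity stay in the residual variance, although three pre-randomization variables that may explain part of them are available at no cost. What is at stake is precision.

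Second, the document calls phase 1 a baseline for everyone, but phase 1 is not the same condition in the two arms. In the feedback arm, moving to phase 2 adds the competition alone. In the control arm it adds feedback and competition at the same moment. A paired test over all participants therefore mixes the Aim 1 effect into the Aim 2 answer. The better feedback works, the more likely the competition is to be credited with an effect it may not have.

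**Working it through.** **1. The stated power.** Inputs from Power analysis: 50 per arm, difference 1200, SD 2000, "using a two group t-test with a 0.05 two-sided significance level".
- Standard error of the difference = 2000 × √(2/50) = 400 steps.
- Noncentrality = 1200/400 = 3.0; with 98 degrees of freedom, power = 84.4%. The stated 84% reproduces.

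**2. Power after adjustment.** Let r be the (multiple) correlation of the covariates with mean phase 1 steps. Residual SD = 2000 × √(1 − r²). Degrees of freedom are taken as 97, for one covariate; a few more covariates change the result negligibly. The protocol gives no r, so it is varied.

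| Assumed r | Residual SD | Standard error | Power for 1200 steps |
|---|---|---|---|
| 0 (as planned) | 2000 | 400 | 84.4% |
| 0.2 | 1960 | 392 | 85.8% |
| 0.3 | 1908 | 382 | 87.6% |
| 0.5 | 1732 | 346 | 92.9% |
| 0.7 | 1428 | 286 | 98.6% |

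The survey is self-reported and completed about one to six months before wear begins, so the rows for 0.2 and 0.3 are the realistic guide for it. The last row would need something closer to a device measurement.

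**3. What the phase 2 change estimates.** Let d be the feedback effect, assumed equal in both phases, and c the added effect of the competition.

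| Group | Phase 1 | Phase 2 | Expected change |
|---|---|---|---|
| Feedback arm | feedback | feedback + competition | c |
| Control arm | no feedback | feedback + competition | c + d |
| Pooled 1:1 | | | c + d/2 |

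With c = 0 and d = 1200 (the design effect), the pooled change is +600 steps.

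**4. How often the pooled test would reject when c = 0.** Assume SD 2000 in each phase and a correlation ρ between a participant's two phase means (not given in the protocol). The SD of change within an arm is 2000 × √(2(1 − ρ)). Pooling adds the between-arm spread, so SD = √(within² + (d/2)²). There are 100 participants and 99 degrees of freedom, and the noncentrality is (d/2)/(SD/10).

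| d | ρ | SD of pooled change | Noncentrality | Rejects, showing an increase |
|---|---|---|---|---|
| 1200 | 0.5 | 2088 | 600/208.8 = 2.87 | 81% |
| 1200 | 0.8 | 1400 | 600/140 = 4.29 | 99% |
| 600 | 0.5 | 2022 | 300/202.2 = 1.48 | 31% |
| 600 | 0.8 | 1300 | 300/130 = 2.31 | 63% |

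**5. Would an untreated week serve as the Aim 2 baseline?** Measured against a week without feedback, the expected change is c + d in both arms. At d = 1200 and c = 0, the false competition change would rise from 600 to 1200 steps, and the one arm that isolates the competition would be lost.

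**6. Cost of using the feedback arm alone.** The standard error of the mean change is 2000/√50 = 283 steps at ρ = 0.5 and 1265/√50 = 179 at ρ = 0.8. With all 100 participants, ignoring the between-arm spread, it would be 200 and 126.

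**The case against.** **On the primary test.** Randomization makes an unadjusted comparison valid. Chance imbalance in habitual activity is ordinary sampling error, which the t test's standard error already covers, and the design meets its stated power. Covariates are often named in a statistical analysis plan, which is not at hand, and nothing shows that the survey correlates even 0.3 with steps. All of this stands. A reader might infer that the primary result is biased or the study underpowered because no baseline steps are taken. The document supports neither. What remains is that it names an unadjusted test while holding usable covariates, so the loss is one of efficiency and may be only a point or two of power.

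**On phase 2.** The protocol says plainly which reference it means, controls do have six weeks without feedback, and the planned between-arm comparison of changes would expose the asymmetry. That also stands, but showing that the arms differ does not make a pooled paired test a test of the competition. A separate plan could specify analysis by arm; the protocol does not, and it names the paired test as the one that answers the competition question.

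A reader might also infer that the fault lies in the feedback arm, whose phase 1 is already treated, and that Aim 2 needs an untreated baseline. The design points the other way. For the added effect of competition, feedback alone is the right reference, and it is the control arm that is confounded. An untreated reference would make matters worse (working, step 5).

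**Conclusion.** The point holds in two parts of different weight.

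The primary analysis is valid and correctly powered but less precise than it could be at no cost. The gain is about 1 to 3 percentage points of power at r of 0.2 to 0.3, and about 9 at 0.5. The size rests entirely on an assumed r.

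The Aim 2 analysis has the more serious weakness. If the paired test is pooled over arms, as the wording allows, it estimates c + d/2. At the design effect this gives +600 steps and a false claim for the competition in about 81% to 99% of trials. Those figures assume a feedback effect of 1200 that is equal in both phases, SD 2000 in each phase and a phase correlation of 0.5 to 0.8. At d = 600 the range is 31% to 63%, and with no feedback effect the problem disappears.

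The feedback arm's own change is free of the unblinding effect. It remains a before-and-after comparison without a concurrent control, so season and waning novelty cannot be separated from the competition.

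**What to change.** 1. **Primary analysis.** Replace the choice between t and Wilcoxon tests with one linear model of mean phase 1 steps per day on arm, adjusted for class year, baseline survey physical activity and sex. Cost: wording only; the data are already collected.
2. **Phase 2.** Stop calling phase 1 a baseline without qualification. Report the phase 2 minus phase 1 change separately by arm, and base the competition conclusion on the feedback arm. Describe the control arm's change as the joint effect of feedback and competition. Cost: wording, plus a conclusion resting on about 50 participants instead of 100, with the wider standard error shown in working, step 6.
3. **Optional.** A week of blinded wear by everyone before feedback is switched on would give a stronger covariate for the primary model. Cost: about one extra week of wear, switching on the feedback arm's devices after it, and matching changes to the 12-week raffle and the rule for keeping the device after 75% wear (Recruitment Procedures). Use that week for the primary model only. As the Aim 2 reference it would mix feedback with competition in both arms.
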